## Methods/design

2

### Study design

2.1

This is a prospective, explorative, observational study. Ethical approval has been obtained from the local ethics committee (University of Kiel (D 427/17; amendment of 12/2023 (Geritz et al., 2020)). The study is in accordance with the Declaration of Helsinki. All participants will receive detailed verbal and written information about the content and procedure of the study.

### Participants

2.2

Participants will be neurogeriatric, defined as > 70 years with a primary neurological disease [participants between 50 and 69 years of age can also be included if they have at least two chronic diseases (> 6 months)] [ Sieber, 2007; Maetzler et al., 2016; Johnston et al., 2019). Other inclusion criteria are the ability to consent to the study and, if applicable, the consent of the legal representative, as well as at least 5 points on the Montreal Cognitive Assessment (MoCA, (Nasreddine et al., 2005)].

### Procedure

2.3

Participants will be recruited at the Department of Neurology, University Hospital Schleswig-Holstein, Kiel, Germany. Participants will be enrolled within the initial 2 days of admission (T1). A subsample of 50 patients who undergo a comprehensive geriatric care (CGC) will be reassessed during the last 2 days of their inpatient stay (T2), which typically lasts 14–20 days. All participants will be provided with multidisciplinary therapy, which will be specific to their individual needs, during the course of their hospitalization. Cognitive function and attention will be evaluated using validated tests (see next section). Sustained attention and neurophysiological parameters will be evaluated using computerized tasks and EEG recordings conducted in a laboratory setting (for an overview of the EEG setup; see Figure 1). The experimental paradigms, including the Go-NoGo and Psychomotor Vigilance Task (PVT), will be presented on a 27-inch screen in a stable low-light environment. Prior to the main tasks, two practice trials of the Go-NoGo task (the first at a slower speed) and one practice trial of the PVT will be conducted. After completing both tasks, a resting-state EEG will be recorded for 5 min with eyes open and 5 min with eyes closed. An overview of the study design and assessment procedure is shown in Figure 2.

**FIGURE 1 F1:**
[figure not shown]
**(A)** Schematic overview of the EEG recording setup. Sustained attention paradigms (Go-NoGo task and PVT) are presented on a 27-inch monitor. Participants wear a 32-channel EEG cap arranged according to the international 10–20 system. Behavioral responses are recorded via a response key, while EEG signals are acquired using an actiChamp amplifier (Brain Products) and streamed to the recording unit via the Lab Streaming Layer (LSL). **(B)** Experimental timeline of the EEG session including practice trials, the Go-NoGo task, the PVT, and resting—state EEG recordings with eyes open and eyes closed.

**FIGURE 2 F2:**

Overview of the study design and assessment procedure of the SENSE-AGE study.

### Clinical assessment

2.4

#### Clinical and demographic data

2.4.1

To obtain a comprehensive description of the neurogeriatric cohort, data will be collected both in medical history and through semi-structured interviews. Functional status will be assessed using the *Activities of Daily Living* (ADL) scale (Katz, 1963), which measures basic self-care abilities. The total score range from 0 to 6, with higher scores indicating greater functional independence. The instrument has shown good reliability and validity in clinical settings, including studies reporting consistent performance characteristics in older adults (Brorsson and Asberg, 1984; Arik et al., 2015). Instrumental activities of daily living will be assessed using the IADL scale from Lawton and Brody (1969). This questionnaire evaluates more complex daily functions and total scores range from 0 to 8, with higher scores reflecting greater autonomy. The scale has shown good construct validity and sensitivity in detecting functional decline in older populations. Geriatric status will be assessed using the *Geriatrie Check* (Hobert et al., 2019), a screening tool designed to identify geriatric patients. The tool covers domains such as cognitive impairments, care dependency, frailty, and premorbid functional status. It has been validated in a cohort of hospitalized neurological patients and demonstrated good discriminative validity (Hobert et al., 2019). Diagnoses, medications, and duration and number of therapy units will be collected as covariates.

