**Methods/design:**

The study “Studying Neurocognitive Systems for Sustained Attention in Neurogeriatrics Patients” (SENSE-AGE) is a prospective, explorative, observational study and will include 120 geriatric participants. At admission, participants will perform a Go-NoGo task, a Psychomotor Vigilance Task (PVT) and resting-state condition during EEG recording, using a 32-channel system. Task-based event-related potentials (ERPs) and frequency-band power will be extracted. Neuropsychological tests characterize global and domain-specific cognition and will examine associations between sustained attention, broader cognitive performance, and EEG parameters. Questionnaires will assess fatigue, sleep, health-related quality of life, and subjective cognition. A subgroup of 50 participants will be re-evaluated at the end of the inpatient stay, after 2–3 weeks of standardized geriatric complex treatment. The main hypotheses of the study are: sustained attention (i) correlates with ERP amplitude and latency; (ii) correlates with EEG power; (iii) improves after an inpatient multiprofessional complex treatment at both the task-performance and neurophysiological level.

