### Data analysis and statistical approaches

2.5

Non-time series data, such as questionnaires, will be partially digitally collected and managed using the Research Electronic Data Capture (REDCap) tool hosted at the University of Kiel (Harris et al., 2009; Harris et al., 2019). REDCap is a secure, web-based software platform designed to support data capture for research studies, providing (1) an intuitive interface for validated data capture; (2) audit trails for tracking data manipulation and export procedures; (3) automated export procedures for seamless data downloads to common statistical packages; and (4) procedures for data integration and interoperability with external sources. Statistical analyses will be performed using JASP (currently Version 0.18.3) (JASP Team, 2024). We will use common descriptive and inferential statistics, as well as appropriate non-parametric statistics, to summarize the baseline data (Fortenbaugh et al., 2015). We will test for normality with Shapiro-Wilk test and Q–Q plots. To assess time-on-task effects, paired *t*-tests or Wilcoxon signed-rank tests will be used to compare reaction times and errors between the first and last quarters of the tasks (Pershin et al., 2023). In addition, correlation analyses (Pearson or Spearman) will be performed to assess the relationship between the number of trials and reaction time. Multiple linear regression will be used to analyze the influence of confounding factors (e.g., age, gender, depression, and cognitive function) on task scores.

Paired *t*-tests or Wilcoxon signed-rank tests will be used for pre-post comparisons to detect changes in clinical variables, as well as behavioral and EEG measures of sustained attention.

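### Medication is to be controlled as an EEG confounder, but the only stated T1–T2 analysis is a paired test that cannot account for a drug change between the two recordings

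*Protocol article*

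**What the plan says.** Hypothesis (iii), in the abstract, is that sustained attention "improves after an inpatient multiprofessional complex treatment at both the task-performance and neurophysiological level". It is tested in the 50 patients measured at both T1 and T2.

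- **Covariates.** Section 2.4.1: "Diagnoses, medications, and duration and number of therapy units will be collected as covariates".
- **Confounders.** Section 2.5.1 lists medication use among the variables to be controlled, together with age, cognitive status and mental disorders. The model given there is an ANCOVA of N200 and P300 measures on task performance.
- **Pre-post analysis.** Section 2.5 names paired t-tests or Wilcoxon signed-rank tests, which "will be used for pre-post comparisons to detect changes in clinical variables, as well as behavioral and EEG measures of sustained attention".
- **Treatment.** The abstract places T2 "after 2–3 weeks of standardized geriatric complex treatment". Section 2.3 says that all participants receive "multidisciplinary therapy, which will be specific to their individual needs", and gives a stay "which typically lasts 14–20 days".
- **Limitations.** Section 3.1 concedes that, without a control group, change in the twice-measured patients cannot be causally attributed to the treatment. It mentions medication as a source of variability in EEG measures.

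**The concern.** The article sets out to control medication and collects the data to do so, but the method it names for change has no place for them. A paired comparison deals well with confounders that are fixed within a patient, such as diagnosis. It does not deal with one that differs between the two sessions. A psychoactive drug that is started, stopped or altered between T1 and T2 may itself move EEG power, ERP measures or reaction times, and that movement becomes part of the mean change. It could be read as improvement after treatment, or it could hide one.

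The therapy units are in a similar position. T1 falls within the first two days of admission, so the therapy delivered during the stay bears mainly on the T1–T2 comparison, where no stated analysis uses it.

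**Working it through.** **Step 1: which stated model could use the covariates for change?**

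- Section 2.5, paired t or Wilcoxon: addresses T1–T2 change; takes no covariate.
- Section 2.5, multiple regression: confounders of task scores; not stated for change.
- Section 2.5.1, ANCOVA: N200 and P300 measures on task performance, adjusted for confounders including medication; not stated for change.
- Section 3, regression and moderation: the relation between EEG markers and behaviour; not stated for change.

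None of these names therapy units. The article also does not say whether medication is recorded again at T2.

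**Step 2: what pairing removes.** For patient i, write the change as D = τ + δX + e. Here τ is the mean change without drug effects, X = 1 if a relevant drug changed between sessions (0 otherwise), and δ is the shift this causes. Stable patient characteristics cancel in the subtraction; δX does not. With a share q of patients changed, the expected mean change is τ + qδ.

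**Step 3: size.** The article gives no alpha, SD of change, drug-change rate or drug effect, so there is no figure of its own to reproduce. Assumptions: n = 50, SD of e equal to 1, τ = 0, all shifts in one direction, two-sided 0.05.

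Mean shift m = qδ; SD of change s = √(1 + q(1 − q)δ²); noncentrality = (m/s) × √50, with √50 = 7.07. Rejection rates come from the noncentral t distribution with 49 degrees of freedom.

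- q = 0.1, δ = 0.2: m = 0.02, s = √1.0036 = 1.002, noncentrality 0.14, rejection rate 0.052.
- q = 0.3, δ = 0.5: m = 0.15, s = √1.0525 = 1.026, noncentrality 1.03, rejection rate 0.173.
- q = 0.5, δ = 0.8: m = 0.40, s = √1.16 = 1.077, noncentrality 2.63, rejection rate 0.731.

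For scale, the change that 50 pairs detect with an assumed 80% power is (1.96 + 0.84)/7.07 = 0.40 SD.

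**Step 4: mixed directions.** Suppose again that 30% of patients change with a shift of 0.5 SD, but 20% shift up and 10% down. The mean shift is 0.20 × 0.5 − 0.10 × 0.5 = 0.05 SD, a third of the 0.15 SD above.

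**Step 5: does unequal length of stay matter to the test?** Assume stays uniform over 14–20 days and an effect proportional to stay that averages 0.4 SD. It then runs from 0.4 × 14/17 = 0.33 to 0.4 × 20/17 = 0.47 SD. In 20,000 simulated studies of 50 pairs, power was 0.79 with equal stays and 0.79 with unequal stays.

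**The case against.** The case against is substantial. The study is declared explorative and observational. Research question (iii) asks whether attention improves after the treatment, and a paired test answers that literally. Section 3.1 already disclaims attribution and leaves the list of other influences open. Section 2.4.1 does not tie its covariates to the T1–T2 comparison, and further models for change may sit in an analysis plan that is not shown. Drug changes during the stay are an inference: the article gives no rate, type or direction. The largest illustration needs half the patients to shift by 0.8 SD in the same direction.

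Most of this stands, and it limits the weight of the point. Two things remain. Section 3.1 treats medication as noise, whereas a change between recordings can act as a systematic shift. And the article does fix its pre-post method, one that cannot deliver the control of medication that section 2.5.1 intends.

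A reader might also infer that the article contradicts itself on how much treatment patients receive. It does not: neither the abstract nor section 2.3 describes an amount, and a standardized programme can have individually chosen content. The wording is ambiguous, not contradictory.

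**Conclusion.** The point holds as a modest improvement to the analysis of hypothesis (iii). Medication is named as a confounder and collected as a covariate, but the stated T1–T2 test cannot use it, and pairing does not remove a change between sessions. The effect on the rejection rate could be negligible (0.05) or large (0.73), depending on assumed shares and shifts that the documents do not fix and on all shifts going one way. That uncertainty is the reason to record drug changes and check their influence.

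Two stronger readings are not supported. A reader might infer that unequal exposure undermines the paired test. Under the assumptions in step 5 it leaves power unchanged, and affects only what the mean change represents and whether a relation with therapy received can be seen. A reader might also take the time between sessions to be one of the collected covariates. Section 2.4.1 does not list it, and duration there most naturally refers to the therapy units; the interval would have to be derived from visit dates.

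**What to change.** 1. Keep the paired test as the main pre-post analysis. At T2, flag any change in psychoactive medication since T1, and preset a sensitivity analysis that repeats the EEG and behavioural comparisons in patients without a change.
2. Optionally, and labelled exploratory, regress the T2 − T1 change on the T1 value, therapy units delivered and days between sessions. State that therapy follows need, so the coefficients are confounded and do not identify a treatment effect.
3. Reconcile the abstract and section 2.3 so that one description of the treatment is used throughout.

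The cost is some wording and one chart check in 50 patients; medications and therapy units are already collected. The downside is a smaller subset. If 30% of patients had a change, 35 would remain, and the change detectable with 80% power would rise from 0.40 to 0.40 × √(50/35) = 0.47 SD. The subset should therefore be read for consistency of the estimate and not for significance.

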#### Cognition

2.4.2

Global cognitive functioning will be assessed using the MoCA, a screening instrument covering multiple cognitive domains. The test yields a total score ranging from 0 to 30, with higher scores indicating better cognitive performance; a score below 26 is commonly used as a cut-off for cognitive impairment. It has good internal consistency (Cronbach’s alpha = 0.83) and a high sensitivity in the detection of MCI (90%) and AD (100%) (Nasreddine et al., 2005).

Processing speed and executive functioning will be evaluated using the Trail Making Test (TMT). TMT Part A primarily assesses visual scanning and psychomotor processing speed, whereas Part B additionally requires task switching and cognitive flexibility, reflecting divided attention and executive control. Performance is measured as completion time in seconds, with longer times indicating poorer performance. The TMT shows good construct validity and sensitivity to executive dysfunction in clinical populations (Sánchez-Cubillo et al., 2009). These instruments are included to describe global cognitive status and executive functioning and will be treated as covariates in regression models. They are not considered direct measures of sustained attention.

Sustained attention will be measured with a 16-min cued Go-NoGo task on a computer [adapted from Pershin et al. (2023)]. Participants will see different pairs of pictures from the categories “animals,” “trees” and “fruits” (see Table 1) and have to react as fast as possible by pressing a button when two pictures with animals are shown (Go condition). In the NoGo condition, participants will see an animal as the first stimulus and a tree as the second stimulus, and have to inhibit their response (see Figure 3). The Ignore and Ignore & Novelty conditions will show two trees in a row or a tree and a fruit. No response will be required in these conditions. The presentation duration (100 ms), the interstimulus interval (1,000 ms) and the inter-trial interval will be controlled and the stimulus presentation will be randomized. Sustained attention performance in the Go-NoGo task will be quantified using several behavioral parameters. Median reaction time (RT) for correct responses in Go trials will serve as an index of sustained attentional performance. In addition, omission errors (failure to respond to Go stimuli, calculated as the proportion of missed Go trials) will be analyzed as indicators of attentional lapses, and commission errors (responses during NoGo trials, calculated as the proportion of false responses) as indicator of inhibitory control failures. Furthermore, discriminability (*d*’) will be calculated based on signal detection theory [*d*’ = Z(hit rate) – Z(false alarm rate)] to provide a bias-independent measure of sustained attention performance (Fortenbaugh et al., 2015).

**TABLE 1 T1:** The four different conditions of the Go-NoGo task.

Condition	Stimulus 1	Stimulus 2
Go	Animal	Animal
NoGo	Animal	Tree
Ignore	Tree	Tree
Ignore and novelty	Tree	Fruit

**FIGURE 3 F3:**
[figure not shown]
Example trials of the cued Go-NoGo task, adapted from Pershin et al. (2023). The division of the trials into distinct time windows (500 ms) allows a later analysis of the individual time segments.

In addition to the cued Go-NoGo task, sustained attention will be assessed using the PVT. In the PVT (computerized version), participants will press a button as quickly as possible when a red number appears on the screen. The PVT is a simple reaction time task that isolates vigilance and is particularly sensitive to attentional lapses and fluctuations in alertness, as reflected by reaction time variability and lapses.

To capture attentional stability over time during the Go-NoGo and PVT, intra-individual variability of reaction times (e.g., standard deviation of RTs across Go trials) will additionally be examined, as increased variability has been associated with reduced sustained attention (Hultsch et al., 2002; West et al., 2002; Macdonald et al., 2006).

The *Alters-Konzentrations-*Test (AKT) was developed as a paper-pencil test for older adults and measures the ability to stay vigilant and concentrated. Including the AKT allows comparison of the experimental data with conventional neuropsychological metrics commonly used in geriatric settings. Retest reliability is good (*r* = 0.75–0.89).

Although the Go-NoGo, PVT, and AKT differ in temporal structure and cognitive demands, all three paradigms require sustained attention over time and are therefore conceptualized as complementary operationalizations. Their joint inclusion allows examination of convergent validity across computerized and conventional assessment formats.

Participants’ perception of their ability to pay attention is measured using the FEDA (*Fragebogen erlebter Defizite der Aufmerksamkeit*) questionnaire (Theml and Romero, 2001), a 27-item self-report questionnaire assessing perceived attentional difficulties in everyday situations. The instrument comprises three subscales reflecting cognitive distractibility and mental slowing, fatigue and slowing in practical activities, and reduced attentional activation. Items are rated on a five-point Likert scale (1: “very often”, 2: “often”, 3: “sometimes”, 4: “rarely”, 5: “never”), with lower sum scores indicating more pronounced perceived deficits. The FEDA discriminated between patients with very mild Alzheimer’s dementia and matched healthy controls with an accuracy of 82% (Theml and Romero, 2001).

#### HrQoL, behavior, sleep and subjective assessment of cognition

2.4.3

In addition to objective behavioral and electrophysiological measures of sustained attention, the study assesses health-related and psychological factors that are known to influence cognitive functioning in older adults. Sustained attention in neurogeriatric populations is embedded within a broader biopsychosocial context, in which affective symptoms, sleep disturbances, fatigue, and perceived cognitive decline may modulate both behavioral performance and neural dynamics. These variables will therefore be included (i) as potential confounders in regression models and (ii) as exploratory correlates of sustained attention performance and EEG parameters (Research Question iv). Participants will be asked to complete the following digitized questionnaires on a tablet.

##### Health-related quality of life

2.4.3.1

HrQoL will be assessed using the *European Quality of Life 5 Dimensions 5 Level Version* (EQ 5D-5L) (Herdman et al., 2011). It records HrQoL on the current day in the domains of mobility, self-care, usual activities, pain/discomfort and anxiety/depression. In addition, participants can rate their general health on a visual analog scale (“0” = worst health, “100” = best health they can imagine).

##### Affective symptoms and fatigue

2.4.3.2

Symptoms of depression will be assessed using the *Depression im Alter* scale (DIA-S) (Heidenblut and Zank, 2010), which consists of 10 items related to the past 14 days. Additionally, anxiety and depressive symptoms will be measured using the *Hospital Anxiety and Depression Scale* (HADS) (Petermann, 2011). The HADS consists of 14 items (7 anxiety, 7 depression), each rated on a 4-point scale (0–3), resulting in subscale scores ranging from 0 to 21. Internal consistencies for both subscales are typically around α = 0.80, and the two-factor structure (anxiety/depression) has been well established. Cut-offs allow classification into normal, borderline and clinically relevant symptom levels.

Fatigue will be assessed using the *Functional Assessment of* Chronic Illness Therapy—Fatigue (FACIT-F) (Montan et al., 2018). The FACIT-F is a validated multidimensional instrument assessing fatigue severity over the past seven days on a 5-point Likert scale. A score ≤ 30 has been widely accepted as a clinical threshold for fatigue (Piper and Cella, 2010). Mental fatigue has been shown to impair sustained attention, increase reaction time variability, and alter frontal EEG activity (Wascher et al., 2014; Möckel et al., 2015; Kunasegaran et al., 2023).

##### Sleep quality

2.4.3.3

Sleep quality over the past 4 weeks will be assessed using the *Pittsburgh Sleep Quality Index* (PSQI) questionnaire (Hinz et al., 2017). The PSQI captures seven components, including subjective sleep quality, sleep latency, sleep duration, sleep efficiency, sleep disturbances, use of sleep medication, and daytime dysfunction, which are combined into a global score. Higher scores indicate poorer sleep quality. State sleepiness at the time of testing will be assessed using the *Karolinska Sleepiness Scale* (KSS), a single-item 9-point scale measuring momentary subjective sleepiness (Geiger Brown et al., 2014).

